## Abstract

**Background:**

The incidence of type 2 diabetes mellitus, a chronic lifestyle disease, and its complications are on the rise. Exercise has been documented as being effective in the management of musculoskeletal pain, depression, and reduction of hyperglycemia in diabetic patients. However, there is no consensus regarding the types of exercise that reduce musculoskeletal pain and depression and improve quality of life as well as respiratory function among individuals with type 2 diabetes.

**Objective:**

The objective of this study is to determine the effects of rebound and circuit training on musculoskeletal pain, blood glucose level, cholesterol level, quality of life, depression, and respiratory parameters in patients with type 2 diabetes mellitus.

**Methods:**

A total of 70 participants are expected to be recruited in this single blind randomized controlled trial. Computer-generated random numbers will be used to randomize the participants into 3 groups, namely, the rebound exercise group, the circuit exercise group, and the control group. Measurements will be taken at baseline and at the end of the 8 weeks of the study. Participants’ musculoskeletal pain will be assessed using the visual analog scale, quality of life will be assessed using the SF 12 Health Survey Questionnaire, depression using the Beck Depression Inventory, respiratory parameters using the spirometer, and biochemical parameters such as glucose level and cholesterol level using the glucometer. Data will be analyzed using descriptive statistics and inferential statistics of multivariate analysis of variance between the groups and paired t test within the group. Alpha will be set at .05.

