
### Sample Size and Power Calculation

The sample size (N) will be determined using Cohen table [29] at alpha=.05 and degree of freedom (µ)=k−1, where k is the number of groups, with effect size f=0.35. From the previous study [17] and power (w) 80%, sample size n=20. Sample size (N) will be 60, and 12 extra participants will be added to make room for attrition. Therefore, the sample size will be 72 participants, and each group will be 24 participants.

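### The Abstract plans 70 participants, but the sample size section derives 72 (24 per group), and nothing reconciles the two totals

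*Protocol article*

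**What the plan says.** The Abstract, under Methods, gives the planned total: "A total of 70 participants are expected to be recruited in this single blind randomized controlled trial". It also names three randomized groups: rebound exercise, circuit exercise and control.

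The section Sample Size and Power Calculation sets out a derivation. Its inputs are a Cohen table at alpha .05, "with effect size f=0.35", and "power (w) 80%, sample size n=20". It continues: "Sample size (N) will be 60, and 12 extra participants will be added to make room for attrition". It concludes: "Therefore, the sample size will be 72 participants, and each group will be 24 participants".

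The attrition allowance is given as a count of 12. No attrition percentage is stated. Nothing in the article explains why the Abstract total differs from the Methods total.

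**The concern.** Both statements look forward to the same quantity, the number to be enrolled, and they disagree. Shortening a protocol into an article can drop detail, but it does not turn 72 into 70. This is therefore a misstatement in one of the two places, and not an omission that a fuller document could supply.

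The planned total is the yardstick by which later readers judge whether the trial met its recruitment target. With two published totals, a final enrolment of 70 or 71 could be reported as meeting the plan or as missing it. The Abstract is also the part most readers see.

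**Working it through.** **Inputs.** Abstract total 70. From Sample Size and Power Calculation: 20 per group, N = 60, 12 extra for attrition, 72 enrolled, 24 per group, f = 0.35, alpha .05, stated power 80%. Number of groups k = 3.

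**The Methods arithmetic, reproduced.**
- 3 × 20 = 60
- 60 + 12 = 72
- 72 / 3 = 24

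Each step agrees with the next.

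**The Abstract figure against that chain.**
- 70 is neither 60 nor 60 + 12.
- 70 / 3 = 23.33, so three equal groups are impossible (24/23/23 is the nearest split), and 24 per group cannot be met.
- The gap is 72 − 70 = 2, and 2 / 72 = 2.8%.

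**Completers if 70 are enrolled.**
- Full allowance used as a count: 70 − 12 = 58.
- Allowance read as a proportion, 12 / 72 = 16.7%: 70 × (1 − 12/72) = 58.3.
- Losses that still leave 60: 70 − 60 = 10, and 10 / 70 = 14.3%.

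The shortfall below 60 therefore arises only if more than 10 participants are lost.

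**Power.** One-way ANOVA omnibus F test with 2 and N − 3 degrees of freedom and noncentrality λ = f² × N = 0.1225 × N. The group size is taken as N / 3, which is fractional at 58 and 70.

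| N analysed | λ | Power |
|---|---|---|
| 58 | 7.105 | 63.7% |
| 60 | 7.350 | 65.4% |
| 70 | 8.575 | 72.9% |
| 72 | 8.820 | 74.2% |

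Enrolling 70 rather than 72 costs 74.2 − 72.9 = 1.3 points if nobody is lost, and 65.4 − 63.7 = 1.7 points if all 12 are lost.

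**The stated 80%.** The same calculation does not reproduce 20 per group. At f = 0.35, alpha .05 and three groups, 80% power needs 28 per group, or 84 analysed. Twenty per group reaches 80% only at f of about 0.415 to 0.42. Raising alpha to 0.10 would still need 22 per group.

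**The case against.** The strongest reply is that the discrepancy is editorial. The Abstract speaks of an expected number, while the sample size section gives a derivation and a firm total, so a reader would treat 72 as operative. The difference is two participants, a 24/23/23 split hardly affects a between-group comparison, and the article does not describe blocking that would guarantee exactly 24 per group even with 72.

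Much of this stands. The practical effect is small, and the unequal split is a consequence of the same discrepancy, not a second fault. But the Abstract gives 70 as a total without any qualifier, and no text presents it as an approximation, so the contradiction remains.

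Three stronger readings are tempting, and the document supports none of them:

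- A reader might infer that 70 necessarily leaves too few completers. The 12 are an allowance and not a forecast; up to 10 losses would still leave 60.
- A reader might infer that enrolment will stop at 70. Nothing in the article makes the Abstract figure a stopping point.
- A reader might infer that the 80% power rests on 60 completers and is lost at 58. With the stated inputs, power at 60 is already about 65%.

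**Conclusion.** The point holds as an inconsistency between the Abstract and the sample size section. One of the two totals is wrong as written, and the internal evidence favours 72, because every step of the derivation leads to it and none leads to 70. That conclusion needs no assumption beyond the article's own figures.

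The size is two participants and 1.3 to 1.7 percentage points of power. The power figures assume an omnibus one-way F test at f = 0.35 with equal groups. The shortfall to 58 completers assumes that the whole allowance of 12 is used.

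The verdict does not extend to 72 being adequate. It is the total the plan derives, but on the plan's own inputs it does not deliver the stated 80%. That is a separate and larger question, which correcting the Abstract leaves open.

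**What to change.** Change the Abstract total from 70 to 72 and add 24 per group, so that one recruitment total appears throughout. This is a one-number correction and adds no participants beyond those the sample size section already plans.

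Separately, recheck the power statement against f = 0.35, alpha .05 and three groups before treating 72 as a confirmed target. If that check changes the total, carry the new figure into the Abstract as well. Any cost in participants would come from that recheck and not from this correction.

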**Results:**

The results of this study will identify the effectiveness of rebound exercise and circuit training, compared with the control, in the management of type 2 diabetes mellitus and on quality of life, musculoskeletal pain, depression, glycemic control, cholesterol level, as well as improvement in respiratory function.

**Conclusions:**

Though different additional strategies such as exercise and dietary and lifestyle modifications exist for the control of type 2 diabetes, they are mostly applied for the control of glucose level. No strategies have been identified for the control of complications associated with diabetes such as musculoskeletal pain, depression, and reduction in quality of life.

**Trial Registration:**

Clinicaltrials.gov NCT03200795; https://clinicaltrials.gov/ct2/show/NCT03200795 (Archived by WebCite at http://www.webcitation.org/6mBgcj6z7)

## Introduction

### Overview

Diabetes is a global epidemic disease [1]. The global prevalence of diabetics is currently estimated to be 415 million and is projected to rise to over 642 million by the year 2040, with Asians suffering the bulk of the total diabetes epidemic [2]. The International Diabetes Federation (IDF) estimated that there were 14.2 million diabetes patients living in Africa in 2015, excluding the 67% of patients that are undiagnosed, and the projection rate is expected to rise to 34.2 million by 2040 [2]. South Africa is among the most populous African countries with the highest number of people with diabetes with 2.3 million people, followed by Democratic Republic of Congo 1.8 million, Nigeria 1.6 million, and Ethiopia 1.3 million. Nearly half of the adults with diabetes live in these countries. In South Africa, the prevalence of diabetes mellitus (DM) is estimated to be about 6%, excluding the undiagnosed cases, whereas 9% of the population has prediabetes. DM accounts for 58 deaths daily and is the fifth highest cause of natural deaths [3]. The highest prevalence of diabetes is among the Indian population (11%-13%), as this group has a strong genetic predisposition to diabetes. This is followed by 8% to 10% in the colored community, 5% to 8% among blacks, and 4% among whites. The prevalence of diabetes in the public health sector of KwaZulu-Natal was found to be 14.3% higher than the national prevalence estimates [3].

Diabetes is a systemic disease that affects multiple body functions and structure. The typical spectrum of problems of patients with DM can now be defined based on the International Classification of Functioning, Disability and Health (ICF). For practical purposes and in line with the concept of condition-specific health status measures, DM problems can be classified as follows: body function as hematological system function, sensation of pain, musculoskeletal system, and respiratory system. On the basis of activities and participation restriction, DM problems can be classified as quality of life (QoL) and psychosocial factors. These will serve as a guide in clinical studies with DM or as a guide to multidisciplinary assessments in patients with DM [4].

In 2004, the US National Health Interview Survey reported that 58% of diabetic patients would have a functional disability [5]. The percentage of diabetic patients with a functional disability will increase as the number of diabetic patients increases and will constitute a major public health problem. Recent data show that the prevalence of musculoskeletal pain (MSKP) manifestations in the hands and shoulders in patients with type 1 or type 2 diabetes is 30%. These manifestations are closely linked to age [6] and prolonged disease duration [7,8].

Musculoskeletal disorders are very common in diabetes and are associated with poor glycemic control and more complications. Assessment of musculoskeletal disorders among diabetics should include an estimate of cholesterol, glycemic control, MSKP, respiratory parameters, and QoL.

People with diabetes are at twice as high a risk of suffering from premorbid depression as the general population [5]. The coexistence of depression in people with diabetes catalyzes serious disease comorbidities, MSKP, decreased respiratory capacity, poor glycemic control which may lead to hyperlipidemia and poor QoL, and escalated health care expenditures [9]. Depressive symptoms are more likely to persist among persons with multiple diabetic-related complications such as musculoskeletal disorders. Increase in pain may lead to increased depression and reduction in respiratory capacity and QoL. Studies have shown that both exercises and pharmacotherapy [10] can decrease depression and improve glycemic control and overall QoL in persons with diabetes and thus, in addition, provide substantial financial savings and improved medical care for these individuals.

Exercise, in addition to diet modification and medication, has long been recommended as one of the 3 main components of diabetic therapy [11]. The low cost and nonpharmacological nature of exercise enhances its therapeutic appeal among type 2 diabetic patients. Published exercise intervention trials [12-15], using different types of intervention, usually have small sample sizes and the findings of their studies have varied. The optimal type, frequency, intensity, and duration of exercise for achieving therapeutic goals in type 2 diabetes are not known. The psychosocial variables and cardiorespiratory-related health of diabetics appear to be underexplored in exercise-related interventions [11]. Moreover, prospective randomized controlled trials (RCTs) on the effects of exercise in the prevention or treatment of musculoskeletal complications and disability seen in diabetes patients are needed [16].

Exercise has been documented as effective in the management of MSKP; however, there is no consensus regarding the type of exercises that improve MSKP. The effectiveness of exercise in reducing MSKP as well as depression and in improving respiratory function among individuals with type 2 diabetes has not been documented.

Rebound exercise is a type of exercise that can aid the management of type 2 diabetes [17] and is likely to improve MSKP and depression. Circuit resistance training (CRT) has recently been documented to be safe in the management of type 2 diabetes; however, its effects on MSKP and depression have not been assessed [1]. Rebound exercise on the mini trampoline moves all parts of the body at once, so it is also called cellular exercise [18]. It may be superior to any other type of exercise as it utilizes gravity and forces of acceleration and deceleration so that at the top of the bounce one experiences weightlessness and at the bottom the weight doubles pulling into the center of the rebounder. Rebound exercise is also a form of aerobic exercise that increases oxygen consumption and stimulates immune response.

Circuit training is a combination of strength training and aerobic exercises. Strengthening exercise is a resistance exercise that helps to keep the muscles flexible and strong and also strengthens the bones. Aerobic exercise, on the other hand, is a less vigorous exercise that increases oxygen consumption; the increase in oxygen consumption helps to burn more calories and stimulates immune response and cardiovascular health [19]. Rehabilitation can assist to retain physical and functional abilities as well as control psychological emotions [20]. Therefore, comprehensive rehabilitation to manage diabetes-related complications that encompasses exercises such as rebound and circuit training may improve glycemic control, reduce depression, and improve QoL and musculoskeletal functions.

### Theoretical Framework

Previous studies have assessed the effect of combined resistance and aerobic exercises on type 2 DM patients and observed significant reductions in HbA_1c_ [21-23]. However, Geirsdottir et al [24] did not observe any favorable changes in fasting glucose or HbA_1c_ in patients with type 2 diabetes. Therefore, there is no consensus on the effect of CRT in type 2 diabetes. Rebound exercise has been documented to be effective in reducing plasma fasting glucose, HbA_1c_, and body mass index (BMI) in type 2 diabetes. It is also simple, inexpensive and enjoyable [23]. Moreover, it has been documented to improve QoL in patients with type 2 diabetes [17]. However, its effect on MSKP, respiratory parameters, and depression has not been documented. Prospective RCTs on the effects of exercise in the prevention or treatment of musculoskeletal complications, cardiorespiratory parameters, and psychosocial variables seen in diabetes patients are needed [16]. In African countries, there is a paucity of reports that describe musculoskeletal disorders in diabetic patients. To the best of our knowledge, no clinical trial has been conducted that compares the effect of rebound exercises and circuit training on MSKP, respiratory parameters, and psychosocial variables among patients with type 2 diabetes. No previous studies had been conducted to assess the effect of any treatment or prevalence of MSKP manifestations in diabetic patients or to evaluate the predisposing factors. This study is, therefore, proposed to determine the effect of rebound exercises and circuit training on MSKP, as well as selected biochemical and psychosocial factors among individuals with type 2 diabetes.

### Objective

The objective of this research is to investigate the effect of rebound exercises and circuit training and compare them to the routine care of type 2 diabetic patients. The objectives of this research are as follows;

To investigate the effect of rebound exercises on glycemic control, cholesterol level, respiratory parameters, pain scores, depression, and QoL among type 2 diabetes patientsTo investigate the effect of CRT on glycemic control, cholesterol level, respiratory parameters, pain scores, depression, and QoL among type 2 diabetes patientsTo investigate the effect of routine care (control group) on glycemic control, cholesterol level, respiratory parameters, pain scores, depression, and QoL among type 2 diabetes patientsTo compare the effect of circuit training, rebound exercises, and routine care on glycemic control, cholesterol level, respiratory parameters, pain scores, depression, and QoL among type 2 diabetes patients.

## Methods

### Study Design

The study is a single-blind, parallel RCT. RCTs are quantitative, comparative, controlled experiments in which investigators study 2 or more interventions in a series of individuals who receive them in random order. The RCT is one of the simplest and most powerful tools in clinical research.

### Participants

The participants for the study will be patients diagnosed with type 2 diabetes by the attending physician at King Edward Hospital. Participants will be considered eligible if they have been diagnosed with type 2 diabetes for at least 4 years and have been on oral hypoglycemic control. They will be recruited consecutively as they are available through the outpatient endocrinology clinic of the hospital by a member of the research team. Only participants with MSKP and depression will be included in the study. They will be screened for MSKP using the Nordic Musculoskeletal Symptoms Questionnaire and for depression using the Beck Depression Inventory (BDI). The participants must be aged between 20 and 55 years. Those within this age limit are considered to be adults with musculoskeletal affectation, as indicated by Nordic Musculoskeletal Symptom Questionnaire, and with at least ≥11 score on the BDI. Only participants who meet the inclusion criteria will be considered for the randomization into the groups. The consent of the participants will be sought before they participate in the study.

Patients will be excluded from the study if they are involved in sporting activities or if their musculoskeletal problems are severe and may prevent them from performing some of the exercises. Moreover, individuals with hypertension, coronary artery disease, or myocardial infarction; or who have had cardiac or abdominal surgery within the previous 6 months; or who have a history of fractures of the spine, hip, knee, or ankle joints; as well as those with lower limb weakness and deformities with a loss of protective sensation in the feet will be excluded. Similarly, pregnancy or lactation, use of insulin, and the presence of retinopathy or nephropathy will make a patient ineligible. Finally, subjects who do not consent to participate will be excluded from the study. Participants who meet the inclusion criteria will be randomized into 1 of the 3 groups of the study.

### Setting

The research will be conducted at the Performance Laboratory of the Department of Physiotherapy, School of Health Sciences, University of KwaZulu-Natal. The participants will be recruited from the King Edward Hospital, Durban. King Edward Hospital is a tertiary hospital that provides specialist services to the people of KwaZulu-Natal. It is located in Durban City, Ethekwini Municipality, KwaZulu-Natal Province, South Africa.

### Study Team

The study team will consist of 4 physiotherapists, of which 2 are clinicians and the other 2 are both clinicians and researchers. The team will also include an endocrinologist who is a physician with 10 years of research experience. In addition, 2 among the physiotherapists will be research assistants and they will administer the treatment. The endocrinologist will screen the patients and ensure that they take the same medications and that they are medically fit, whereas the researchers will screen the participants to ensure that they meet the inclusion criteria.

### Intervention

The study will comprise 3 groups; the rebound exercise group, the circuit resistance exercise training group, and the routine care group (the control). The routine care group will undergo one exercise training after 8 weeks of enrollment. Participants will be monitored for subjective fatigue, dyspnea, respiratory distress, profuse sweating, or unsteady gait during the exercise activities, as these may be indications that they have reached maximum exertion.

### Rebound Exercise Group

Participants randomized to this group will be instructed on the proper techniques of the desired movements (hopping) on the rebounder. All instruction and training will be provided by the research assistants who are physiotherapists practicing in South Africa. They will teach the participants how to rebound during the session. To ensure exercise endurance, patients allocated to this group will complete a 6-min walk test (6MWT), as prescribed by the American Thoracic Society [25], which will be conducted along a straight 40-m Department of Physiotherapy passageway. On successful completion of the 6MWT, patients will be given an opportunity to familiarize themselves with the equipment. Each participant will undergo 3 sessions a week for 8 weeks, with each session lasting between 15 and 25 min.

The exercise will involve bouncing on the center portion of a mini trampoline (2013 Portable Model Half-Fold Cellerciser) with feet slightly apart and knees in full extension. Each foot strike equals one step or bounce with step height. This will be defined as the distance between the foot at a maximum height of the jump and the bed of the center of the trampoline ranging between 10 and 15 cm [23]. Exercise durations were set at 5-min intervals with 3-min rest periods. Each exercise program session will last 15 min with 9 min of rest for the first 4 weeks, progressing to 25 min with 15 min of rest in the subsequent 4 weeks, 3 times per week over 8 weeks.

Bouncing frequency will be determined by signals from a metronome and will be set at between 90 and 120 bounces per minute. Heart rate training zone will be maintained during the exercise at a moderate intensity of 40% to 60% and will be calculated using the Karvonen formula ([heart rate reserve×training percentage]+resting heart rate) [23]. The heart rate will be monitored using the heart rate monitor (Polar Electro Oy) that will display the participant’s heart rate and emit a warning signal if the heart rate goes outside the prescribed training zone, thus serving as a guide and indicator for the participant to adjust the steps and bounce while on the trampoline. In addition, the Borg scale will be used to assess the rate of perceived exertion.

